## Abstract

**Background:** An urgent need exists for evidence-based dietary guidance early in life, particularly regarding protein intake. However, a significant knowledge gap exists in the effects of protein-rich foods on growth and development during early complementary feeding.

**Methods:** This is a randomized controlled trial of infant growth and gut health (primary outcomes). We directly compare the effects of dietary patterns with common protein-rich foods (meat, dairy, plant) on infant growth trajectories and gut microbiota development (monthly assessments) during early complementary feeding in both breast- and formula-fed infants. Five-month-old infants (up to *n* = 300) are randomized to a meat-, dairy-, plant-based complementary diet or a reference group (standard of care) from 5 to 12 months of age, with a 24-month follow-up assessment. Infants are matched for sex, mode of delivery and mode of feeding using stratified randomization. Growth assessments include length, weight, head circumference and body composition. Gut microbiota assessments include both 16S rRNA profiling and metagenomics sequencing. The primary analyses will evaluate the longitudinal effects of the different diets on both anthropometric measures and gut microbiota. The secondary analysis will evaluate the potential associations between gut microbiota and infant growth.

**Discussion:** Findings are expected to have significant scientific and health implications for identifying beneficial gut microbial changes and dietary patterns and for informing dietary interventions to prevent the risk of overweight and later obesity, and promote optimal health.

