#### Randomization

Upon enrollment, participants are randomized into one of four groups, differentiated by source of protein-rich foods they consume (meat, dairy, plant or control group). A stratified random sampling design is used where the strata are defined by mode of feeding (breastfed or formula-fed), sex (male or female) and mode of delivery (cesarean or vaginal delivery). The four feeding groups are randomized within each strata in groups of four so each diet (Meat, Dairy, Plant, Reference) occurs exactly once per four enrollments. Given our rolling recruitment strategy over 4 years, this ensures that the initial randomization of group within each strata is close to balanced and that there is little to no relationship with the order of recruitment. A stratified randomization design controls for possible confounding variables and results in an increase in power.

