### Dietary Intervention

Participants in the three intervention groups are asked to avoid protein-rich foods from other assigned groups (30) and consume protein only from their assigned group. All complementary foods, including infant cereal, low-protein fruits and vegetable purees, and designated protein-rich foods are provided to the three intervention groups. For formula-fed infants, the same brand cow-milk based infant formula is provided. The most recent NHANES report showed that the median protein intake of US infants 6–11 months (31) is 10% total energy or 2.5 g/kg/d. This quantity is used as the targeted total protein intake. Caregivers of infants in the reference/control group are given compensation to purchase complementary foods. Based on weight recorded at the visit and the reported formula/breastmilk intake, a recommended amount of meat- dairy- or plant-based food will be provided to caregivers to approximate a total protein intake of 2.5 g/kg/d. This estimation is updated every month. A sample diet plan is in Table 1, based on a formula-fed infant with a 60th percentile weight-for-age at 9 months.

**Table 1 T1:** Examples of diet plans for the three intervention groups^a^.

	**Food item**	**Protein**	**Calorie**
Total	Total calorie needs		~650 kcal/d
	Total protein (2.5 g/kg/d)	21 g/d	84 kcal/d
Formula (not restricted)	Formula 18 ounces	9 g/d	400 kcal/d
Dairy group^b^	1 Yogurt (Yobaby^®^)	4 g/d	80 kcal/d
	Cheese (shredded) (Horizon^®^)	6.5 g/d	80 kcal/d
	Others (e.g., 1 Beech Nut^®^ zucchini and banana blend; or one servicing of fortified rice cereal)	1 g/d	
Meat group^b, c^	1.5 jar of ham and gravy (Gerber^®^)	10 g/d	80 kcal/d
	Others (e.g., 1 Beech Nut^®^ zucchini and banana blend; or one servicing of fortified rice cereal)	1 g/d	
Plant group^d^	1.5 vegetable pouch (e.g., Ella's kitchen^®^ four bean feast)	5 g/d	90 kcal/d
	1.5 vegetable pouch (e.g., Earth's best^®^ spinach lentil)	5 g/d	50 kcal/d
	Others (e.g., 1 Beech Nut^®^ zucchini and banana blend; or one servicing of fortified rice cereal)	1 g/d	
Reference group	No restriction (observational group and will follow standard of care)		

a *These estimates are based on an exclusively formula-fed 9-month-old female with a 8.5 kg body weight which is ~60th percentile weight-for-age*.

b *Both Dairy and Meat groups are advised to avoid plant foods of relatively high protein contents (a list will be provided). Cheese will be shredded before providing to the infant*.

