### Statistical Approach

Aim 1: Using ANOVA for continuous variables and chi-squared test for categorical variables, we will assess whether matching and randomness held by testing whether potential confounders (e.g., feeding mode, maternal height, maternal BMI, education, sex, race/ethnicity, and smoking during pregnancy) differ between groups. Variables with a *p* < 0.05 and those that have a strong association with the outcome of interest are included in future models. To model the relationship between diet, time, and diet by time interaction and LAZ and WLZ, we use LME model with random effects by subject. This structure explicitly models multiple time points per infant and can adjust for changes of cofounders during the intervention (e.g., a participant changed from breastfeeding to formula feeding at 9 months). Given a significant diet by time interaction, we will test pairwise differences in growth trajectories using Tukey's multiple comparisons.

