Aim 2: We model the effects of diet on the gut microbiota at the end of the intervention and longitudinally, incorporating likely covariates and potential cofounders. 16S amplicon sequencing and metagenomic sequencing will each generate tables of annotated sequence counts. Both datasets will be used to model the diet's impact on microbiota taxonomic composition and functional capacity (i.e., genes and pathways identified through shotgun metagenomics) over the course of the intervention. To evaluate differences in overall taxonomic/functional community composition (i.e., beta-diversity), we use the Microbiota Regression based Kernel Association Test (MiRKAT). MiRKAT models the microbiota using phylogenetic kernels to account for differences in microbial profiles (16S or metagenomics count data) (41). As different measures of dissimilarity are optimal under different conditions, optimal-MiRKAT allows multiple dissimilarity metrics to be tested simultaneously. To model microbial taxonomic and functional profiles over time, we use two methods recently proposed (42). First, we use a bi-exponential distribution to summarize microbiota diversity curves over time. To make inferences, we will incorporate the distribution into a hierarchical model with a random intercept to account for multiple measurements for each person. This approach will model changes in individual taxa, both the rare and common, over time. Additionally, we will evaluate longitudinal changes in common alpha-diversity metrics (e.g., richness, evenness, Shannon diversity, and effective species [e.g., Hill's number (42)]). Finally, we use the control group to build a gut microbiota maturation model via a random forest approach as previously described (24) and compare the intervention groups to this model.

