Aim 3: We use LME on growth Z scores and the microbiota over time with random effects by subject, and include group as a covariate. We also complete secondary analyses stratified by group to identify relationships between Z scores and microbiota that differ by group. We will use microbiota diversity measures and relative abundances of individual taxa and genes/pathways to model diversity and composition of the microbiota. We also include necessary confounders, e.g., change from breastfeeding to formula. To evaluate whether taxonomic and/or functional features of the microbiota mediate the relationship between diet and growth, we use a method and R package called MedTest (43). As in classic mediation analysis, MedTest evaluates three models (44). In reference to Figure 2, the first model estimates the direct path between protein-rich foods and the gut microbiota and implements as part of Aim 1 using MiRKAT. The second model estimates the path between protein-rich foods and infant growth and will be implemented using a standard linear model in R. The third model estimates the path between protein-rich foods and growth controlling for the path between gut microbiota and growth and will be implemented using MiRKAT. Using these three models, MedTest tests for significances of the mediation effect of the gut microbiota. Since it is unknown which microbiota features may mediate the relationship, MedTest implements multiple microbiota distances: unweighted (45), weighted (46), and generalized UniFrac (47) as well as Jaccard and Bray-Curtis distances. To ensure a well-controlled type-I error rate, MedTest uses a modified permutation procedure to arrive at an omnibus test over all distances.

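### The Aim 1 diet model is said to be able to adjust for feeding changes after randomisation; these cannot confound the assigned diet, and adjusting for them can bias the randomised comparison

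*Protocol article*

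**What the plan says.** The Abstract places randomisation at the start of the intervention: five-month-old infants "are randomized to a meat-, dairy-, plant-based complementary diet or a reference group (standard of care) from 5 to 12 months of age". Under Randomization, the "strata are defined by mode of feeding (breastfed or formula-fed), sex (male or female) and mode of delivery (cesarean or vaginal delivery"), so feeding mode at entry is already handled by design.

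Under Statistical Approach, Aim 1, the diet analysis is specified thus: "To model the relationship between diet, time, and diet by time interaction and LAZ and WLZ, we use LME model with random effects by subject". A significant diet-by-time interaction leads to Tukey pairwise comparisons of the growth trajectories. The next statement about the model is that it "can adjust for changes of cofounders during the intervention (e.g., a participant changed from breastfeeding to formula feeding at 9 months").

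Aim 3, which relates growth Z scores to the microbiota, is firmer about the same variable: "We also include necessary confounders, e.g., change from breastfeeding to formula".

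Nothing in the article limits the Aim 1 diet comparison to baseline variables or labels adjustment for later feeding changes as a sensitivity analysis.

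**The concern.** The example is classified wrongly. A confounder of the diet effect must precede or influence which diet an infant receives. Here the diet is assigned by chance at 5 months, so a feeding change four months later cannot do that. It is a post-randomisation variable that diet may influence.

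At stake is the main strength of the trial for its growth outcomes. A model that conditions on the feeding change may no longer estimate the effect of being assigned to meat, dairy, plant or reference. It may estimate part of that effect, or a mixture of the effect and differences between infants who did and did not change feeding. An analysis plan that followed the article's wording would carry this into the main growth comparison.

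**Working it through.** The article gives no figure for feeding changes, so there is none to reproduce. The check sets the passages side by side and then shows what any bias depends on.

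**1. Timing.** Randomisation is at 5 months (Abstract, Study Design), the example change is at 9 months (Statistical Approach, Aim 1), and the intervention ends at 12 months. The change therefore falls 9 − 5 = 4 months after assignment.

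**2. Role of the variable.** Let A be the assigned diet (a contrast of two arms), S(t) whether the infant has changed to formula by age t, Y(t) the growth Z score, and U the unmeasured causes of both feeding change and growth. Allocation is random within strata, so neither S nor U influences A. An arm difference in S is then either chance, which the unadjusted test already allows for, or an effect of diet. Neither calls for adjustment to make the comparison valid.

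**3. Loss of part of the effect.** Suppose there is no U, diet has effect δ other than through feeding change, feeding change has effect β on Y, and the proportions changed by age t are p1 and p0.
- Total effect of assignment at age t: δ + β(p1 − p0)
- Coefficient of A after adjusting for S: δ
- Part removed: β(p1 − p0)

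For illustration only, with β = 0.3 SD (an assumption; the documents give neither β nor the proportions):

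| p1 − p0 (assumed) | part removed |
|---|---|
| 0 | 0.3 × 0 = 0 |
| 0.10 | 0.3 × 0.10 = 0.03 SD |
| 0.20 | 0.3 × 0.20 = 0.06 SD |
| 0.30 | 0.3 × 0.30 = 0.09 SD |

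Feeding changes accumulate with age. A difference between arms would therefore enter the diet-by-time term, which is the term that opens the pairwise tests.

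**4. A path through unmeasured causes.** If A and U both influence S, then A and U are in general associated among infants with the same S, although randomisation made them independent. The adjusted coefficient of A then picks up part of U's effect on growth, even when diet has no effect at all. If A does not influence S, this path stays closed.

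**5. Is an effect of diet on feeding change plausible here?** Under Dietary Intervention, the amount of study food is revised monthly, "Based on weight recorded at the visit and the reported formula/breastmilk intake", so solids and milk are linked. Caregivers feed the assigned foods themselves. For formula-fed infants, "the same brand cow-milk based infant formula is provided", so a change to formula also alters the dairy protein that the trial is studying. This makes a link plausible; it does not show one.

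**The case against.** **The wording is permissive.** The article says the model can adjust, not that it will. The potential confounders listed just before are baseline characteristics, and the final covariate list commonly sits in an analysis plan that is not shown. This stands as a limit on severity. It does not remove the point, because the article offers a post-randomisation change as an example of a confounder in the diet model. That is a wrong statement rather than a missing detail.

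**The bias needs a premise the documents do not supply.** It is zero unless diet changes feeding. Free formula is a weak reason to expect arm differences: Study Design lists formula for formula-fed or mixed-fed infants alongside both the study foods and the reference group's vouchers, and Table 1 does not restrict it. This stands.

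**A reader might infer a known inflation of the type I error.** Sizeable figures can be produced by simulating one growth measurement regressed on diet and a yes/no feeding change, with assumed rates and an assumed shared cause. The documents do not support using them. The planned model is a repeated-measures one with random effects by subject. There, the coefficient of a time-varying feeding change draws largely on contrasts within infants, so much of a stable shared cause is absorbed. Bias could be far smaller than in the one-measurement model. The loss of a mediated effect in step 3 is not removed by the random effect.

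**A reader might extend the point to Aim 2.** That text speaks only of "incorporating likely covariates and potential cofounders" and names no post-randomisation variable. It is compatible with baseline covariates, so the extension is not supported.

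**Time-varying feeding has legitimate uses.** In Aim 3 the exposure is the microbiota, which is not randomised, and a feeding change can be a real confounder. That use is not criticised.

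**Conclusion.** The point holds for the Aim 1 diet comparison of LAZ and WLZ. A change from breast to formula feeding at 9 months cannot confound a diet randomised at 5 months. Adjusting for it can remove part of the diet effect or open a path through unmeasured causes of feeding change and growth.

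The bias is conditional on the assigned diet affecting feeding changes. Its direction and size cannot be derived from the documents; the figures in step 3 only show how one component scales under an assumed effect. The stronger reading, that the planned analysis is biased by a known amount, is not supported. Adjustment for baseline feeding mode is sound. This should be fixed before growth data are analysed by arm, but it is not a defect in the design or the randomisation.

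**What to change.** State that the main Aim 1 diet comparison adjusts only for variables fixed before randomisation, including baseline feeding mode, sex and mode of delivery as stratification factors. Report changes in milk feeding by arm and age as a result in their own right. Keep adjustment for time-varying feeding for a sensitivity analysis labelled as such, and for the Aim 3 microbiota–growth models.

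The cost is about one sentence in the analysis plan. No new data are needed, since feeding is already recorded at the monthly visits, and the sample size does not change. The only thing given up is that the feeding-adjusted diet result becomes supportive rather than main.

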### Participants

Participants are being recruited in the metro Denver area from households with 3–4 month-old infants via direct mailing by Colorado Department of Public Health & Environment (CDPHE) which has access to the birth registry. Up to 300 infants will be recruited (75/group) to have at least 240 completers (60/group), based on a conservative estimate of 20% attrition.

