### Follow-Up Procedures: Home Visits

Monthly home visits at ages 6, 7, 8, 9, 10, and 11 months of age (±7 days) are conducted for each participant by one or two study coordinators. At each home visit, coordinators collect the following: stool sample (pre-collected by parents within 48 h before the visit), anthropometric measures (weight, length, head circumference), health questionnaire, 3-day diet record, food intake log, and breastmilk collection if the participant consumes breastmilk. The 9-month diet record is a weighed 3-day diet record. Caregivers also conduct test weighing again at 9 months if the participants consume breastmilk. Study coordinators also deliver study food (intervention groups) or food voucher (reference group) at the visit. Growth parameters are plotted on the infant's growth chart and Z-scores are calculated.

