### Primary Outcomes

1) *Infant growth*

Pediatric nurses at the Children's Hospital Colorado CTRC (at baseline, 12 and 24 months) and study coordinators (at monthly home visits) obtain a series of infant anthropometric measurements. These measurements including weight (Seca^TM^ 337 infant scale), length (obtained in recumbent position using an infant stadiometer), and head circumference-for-age (Seca infant head circumference measuring tape). Growth Z scores are calculated using length and weight based on WHO/CDC standards (32).

2) *Body composition and total energy expenditure at 5 and 12 months of age*

At baseline and 12 months, a pre-dose urine sample is collected to document basal enrichment of ^2^H and ^18^O, then 0.1 g/kg body weight 99% enriched ^2^H_2_O and 0.3 g/kg 10% enriched H${}_{2}^{18}$O are orally administered. Caregivers are asked to collect one daily sample for 7 days post-dosing. Urine samples are analyzed for ^18^O and ^2^H enrichment by Off-Axis Integrated Cavity Output Spectroscopy (OA-ICOS, Los Gatos Research Inc., Mountain View CA) (33). Isotope dilution space will be calculated via the standard equation of pre-dose and zero-time intercept enrichment via back-extrapolation, which is validated in infants (34). Total body water will be calculated from dilution space × 1.04 to account for water exchange in non-aqueous tissues. Finally, total fat-free mass will be obtained from total body water ÷ age/sex-specific hydration factor (i.e., 79% for 6-month-old infants). CO_2_ production, obtained from the fractional turnover rates of ^2^H and ^18^O (35), is converted to total energy expenditure via Weir equation (36).

3) *Gut microbiota*

Caregivers will obtain a fresh stool sample each month of participation (5–12 months of age) and one at 24 months. 16S rRNA gene amplicon sequencing (37–39) will be performed on all samples to profile fecal bacterial communities. Following sequence QA/QC (37–39), 16S rRNA gene sequences are classified using the SINA/Silva classifier.

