### Power Calculation and Sample Size Justification

We hypothesize that both the gut microbiota and infant growth trajectories are dependent on types of protein-rich foods consumed. We will recruit up to 75 infants/arm and use a conservative 20% attrition which results in 60/group (total completers *n* = 240). Sample size and power justification are from the longitudinal models with feeding group as the predictor and either gut microbiota (i.e., diversity and *Ruminococcus* abundance) and growth (i.e., linear growth parameter LAZ, overweight parameter WLZ and growth velocity using the WHO 0–24 months standards) as the outcomes. We completed power simulations (1,000 replicates) using a linear mixed-effects model (LME) with random effects by subject. For the simulations, we used parameter estimates (e.g., fixed and random effects) from our randomized pilot study on the gut microbiota and infant growth trajectories after receiving meat- or dairy-based complementary diet (30). We simulated a variety of scenarios assuming that Plant had microbiota and growth outcomes that were either worse than Dairy, between Dairy and Meat, or the same as Meat. *To be conservative, we estimated power after increasing the within-group variability by 50%*. The power is above 80% in all simulated scenarios (80–90%) where the effect size was simulated to be at least 50% of that observed in our pilot study (30). The power of most simulation scenarios was below 80% when the effect size was 25% of that observed in the pilot study (30).

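### The Aim 2 longitudinal microbiota model names only a random intercept for eight or nine repeated samples; if infants' rates of change differ or neighbouring months correlate, diet comparisons of change over time will be anti-conservative

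*Protocol article*

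**What the plan says.** Statistical Approach, Aim 2, opens: "We model the effects of diet on the gut microbiota at the end of the intervention and longitudinally". For the monthly course, it summarises diversity curves with a bi-exponential distribution and, for inference, will "incorporate the distribution into a hierarchical model with a random intercept to account for multiple measurements for each person". The same model is meant to describe change in individual taxa. The random intercept is thus the stated device for repeated measurements, and no other within-infant structure is named.

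The number of repeats comes from Primary Outcomes: "Caregivers will obtain a fresh stool sample each month of participation (5–12 months of age) and one at 24 months". That is eight samples during the intervention plus one later. The home-visit schedule agrees: six home visits at 6 to 11 months, plus the 5- and 12-month clinic visits.

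The other longitudinal models are worded more loosely. For growth (Aim 1), "we use LME model with random effects by subject". The power simulation was run "using a linear mixed-effects model (LME) with random effects by subject". Neither says whether slopes are included. Aim 1 names a diet-by-time term. Aim 2 does not, and it does not say how time is coded.

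**The concern.** A random intercept alone assumes that any two samples from one infant are equally correlated, however far apart, and that all infants in an arm share one rate of change once covariates are accounted for. Both are strong assumptions between 5 and 12 months. The article itself expects infants to differ in microbiota maturity, to be breast- or formula-fed, and sometimes to change feeding mode during the intervention.

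The primary hypothesis includes a difference between diets in gut microbiota during complementary feeding, so differences in change over time are of direct interest. Those are the comparisons whose standard errors suffer most under an intercept-only model. Gut microbiota is a primary outcome, and p-values for diet differences in diversity curves or individual taxa could be too low.

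**Working it through.** **Inputs from the article.** Four arms; 75 recruited and 60 completers per arm; eight monthly samples, plus one at 24 months; random intercept for the Aim 2 longitudinal model.

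**Reproducing the stated figure.** 60 / (1 − 0.20) = 75 per arm, 4 × 75 = 300 recruited, 4 × 60 = 240 completers. This matches. The stated 80–90% power cannot be reproduced, because the pilot effects, SDs and variance components are not given. No type I error rate is stated for Aim 2.

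**Assumptions.** Alpha 0.05; complete balanced data; a linear-Gaussian outcome as a stand-in for the bi-exponential model; no diet effect. Let r be the between-infant SD of the monthly slope divided by the residual SD. The article gives no value for r, so a range is shown.

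**Formula, linear age, eight visits.** The sum of squares of age about its mean is Sxx = 42. In units of the residual variance:

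- true variance of one infant's fitted slope: 1/42 + r²
- variance the random-intercept model uses: 1/42 + r²/7, because it spreads the slope variation over the 7 within-infant degrees of freedom
- understatement factor: k = (1 + 42r²) / (1 + 6r²), which cannot exceed 42/6 = 7
- type I error of the 3-df diet-by-time test: P(χ²₃ > 7.815/k)

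For example, r = 0.1 gives k = 1.42/1.06 = 1.34, and r = 0.2 gives k = 2.68/1.24 = 2.16.

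| r | k | Linear age, formula | Linear age, simulated | Visit as category (21 df), simulated | Random slope, simulated |
|---|---|---|---|---|---|
| 0 | 1.00 | 5.0% | 4.9% | 5.0% | 4.7% |
| 0.02 | 1.01 | 5.3% | 5.3% | 5.1% | 5.1% |
| 0.05 | 1.09 | 6.6% | 6.4% | 5.0% | 5.0% |
| 0.1 | 1.34 | 12.0% | 12.0% | 5.4% | 4.8% |
| 0.2 | 2.16 | 30.6% | 30.3% | 7.0% | 4.9% |
| 0.3 | 3.10 | 47.2% | 48.1% | 9.6% | 5.0% |
| 0.5 | 4.60 | 63.7% | 63.9% | 13.6% | 5.0% |

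The simulations used 10,000 trials per row. The first two simulated columns keep the random intercept only. The last analyses each infant's own slope, which is what adding a random slope amounts to in balanced data. With linear age the error passes 10% at r ≈ 0.085 and 20% at r ≈ 0.146. A single pairwise slope contrast is milder: 9.0% at r = 0.1, 18.2% at 0.2 and 36.1% at 0.5.

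**With the 24-month sample in the same linear trend.** Sxx rises to 255.6 and the 3-df test gives 16.1% at r = 0.05 and 40.7% at r = 0.10.

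**Serial correlation without slope variation.** Let R be the AR(1) correlation matrix of the eight residuals and t the centred age. Then k = (t′Rt/42) / [(8 − 1′R1/8)/7].

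- Correlation 0.3: k = 1.416/0.899 = 1.57, type I error 17%.
- Correlation 0.5: k = 1.679/0.785 = 2.14, type I error 30% (29–31% in separate simulations).

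Analysing infants' own slopes stays near 5% in both cases.

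**The case against.** The best counter-argument is that the calculation does not use the model quoted. Aim 2 describes a bi-exponential hierarchical model from a cited method that is not at hand. It writes out no diet-by-time term and does not say that time is linear. This stands: the figures show the mechanism and its plausible range, and do not predict this trial's error rate.

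Time coding matters greatly. With an assumed residual SD of 0.35 and slope SDs of 0.05 to 0.10 per month (r from 0.14 to 0.29), linear age gives roughly 20% to 45%, but visit as a category gives only about 5% to 9%. This also stands.

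A full plan might add further terms to the random intercept. That is possible, but the article goes beyond silence: it names a structure and says what it is for.

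Four stronger readings are tempting and are not supported:

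- *That the tests will reject far more than 5% of the time.* This needs a value of r or a serial correlation that the article does not give. Below r of about 0.05 the inflation from slope variation is slight over the eight visits.
- *That differing slopes are treated as free of noise.* Part of the slope variance enters the residual, which is why k is capped at 7 for eight visits.
- *That all of Aim 2 is affected.* MiRKAT, the random-forest maturation comparison and end-of-intervention comparisons do not rest on this model. The random effects for the alpha-diversity metrics are not stated. Shotgun data exist only at baseline and 12 months; with two samples per infant, a random-intercept test of change uses the right variance and a random slope cannot be separated from the residual.
- *That Aim 1 has the same fault.* Its unspecified subject-level random effects may already include slopes. That is detail commonly left to the analysis plan and is not an error.

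**Conclusion.** The point holds conditionally. The covariance structure stated for the Aim 2 longitudinal model is valid for comparing change over time only if infants within an arm share a slope and residuals are independent across months. The article defends neither assumption. If either fails, standard errors are too small. In the stand-in the consequence runs from none to a type I error several times the nominal level with linear age, and is modest with visit as a category. Which of these applies cannot be settled from the article, which gives no variance components, time coding or alpha for Aim 2. The change is worth making because the outcome is primary and the protection costs little.

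**What to change.** For the Aim 2 longitudinal models on the monthly 16S data, specify one of the following:

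- an infant-level random slope for age in addition to the random intercept;
- visit as a category with an AR(1) or unstructured within-infant covariance;
- infant-clustered robust standard errors.

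Allow a simpler structure only after documented non-convergence. State how time is coded, which term carries the diet comparison, and whether the 24-month sample enters the same trend. The sponsor already holds fixed- and random-effect estimates from its pilot, used for the power simulation, and could check whether they inform the likely slope variation. The two-time-point shotgun analysis needs no random slope, and nothing in Aim 1 needs correcting on this ground.

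The cost is a few sentences in the plan, somewhat wider intervals and some convergence work, particularly for rare taxa. If slopes prove equal, the random-slope analysis still has about 5% type I error in the stand-in.
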